#### Secondary measures

All of the following secondary measures will be completed at baseline and at the end of the three-week study period.

##### Carer-resident's quality of relationship

Family carers will be asked to rate the overall quality of their relationship with their relative on a five-point Likert scale. They will also complete the 15-item Mutuality Scale of the Family Caregiving Inventory which measures the positive aspects of relationship quality using the dimensions love, shared pleasurable activities, shared values, and reciprocity [28]. Examples of items are "How close do you feel to your relative?" and "To what extent do you enjoy the time the two of you spend together?" The scale has high internal consistency (*alpha *0.91-0.95) in studies of family care [29] and scores correlate highly with carer role strain [28] and the stages of Parkinson's disease [29].

##### Carer's mastery

Carers will complete five items of the Pearlin Mastery Scale matching the items administered at the end of every study visit but using the scale's original wording describing global mastery [26]. These items include, "I have little control over the things that happen to me" and "There is really no way I can solve some of the problems I have". This shortened scale has a high internal consistency with an *alpha *of 0.72 [27].

##### Carer's mood

The widely used Center for Epidemiological Studies Depression Scale (CES-D) is a 20-item self-report scale of depressive symptoms covering mood, self-esteem, energy, relationships, sleep and appetite [30]. A cut-off point of ≥ 16 is often used to denote clinically relevant depression. Internal consistency is high with an *alpha *of 0.85-0.92 and scores correlate well with clinicians' ratings and other measures of depression, distress and negative affect.

##### Carer's quality of life

The Carer-QoL [31] is a short, seven-item self-report questionnaire concerning difficulties with physical and mental health, finances and social support. Scores correlate highly with measures of carer strain, carer burden and other global measures of their quality of life including the EuroQol-5D. Feasibility has been reported as excellent with 98% of subjects completing all items.

##### Other measures

Measures collected at baseline will include residents' and carers' socio-demographic details, type of relationship (friends and neighbours can be included if they meet criteria), duration of caring, the frequency and length of visits, and quality of the pre-morbid relationship. We will abstract the date of admission to the facility from the resident's file and will complete the Clinical Dementia Rating Scale (CDR) [32] and Cohen Mansfield Agitation Inventory [33] with a staff member to establish dementia severity and level of agitation.

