Dementia may also inflict negative consequences for family members of the individual with dementia [11]. Frequently reported adverse consequences of caring for relatives with dementia include physical health problems, depression, social isolation and financial burden [12]. These stresses might be expected to diminish following admission to a residential facility where care tasks are undertaken by paid staff. In reality, stress levels often remain high, with only a change in the source of burden [13,14]. New stressors may include the practicalities of visiting, tension with staff regarding care roles, concerns about care and continuing costs [15]. Carers possibly also experience guilt and difficulties relinquishing their role as primary supporter [16,17]. In addition, visits to the facility can prove unsatisfying, especially if the resident is anxious, agitated and increasingly more confused. There are fewer opportunities for easy communication, shared activities and contentment in the relationship [18,19]. Interventions to ease this transition have included carer education and support groups [20]. While promising, they considered the family carer and resident separately, overlooking the loss of relationship between the two, particularly significant for spouses [15,21]. Preserving and enhancing this relationship through meaningful activities can restore a sense of competence and self-determination for family carers [22] and improve the well-being of both parties [23]. An activity program delivered by family carers to relatives with dementia living in the community resulted in large increases in carers' confidence through perceived enhanced skills and personal control as well as enhanced engagement and mood of the individuals with dementia [24].

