### Setting

The study will be conducted in mainstream and psychogeriatric aged care facilities in the state of Victoria, Australia. Preference will be given to larger facilities (≥ 60 beds).

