### Outcomes measures

#### Primary measure

##### Quality of visits

We will ask carers to rate their overall satisfaction with each study visit on a 5-point Likert scale. In addition, they will complete a truncated version of the Pearlin Mastery Scale [26] adapted to care-related situations [27], focussing on their sense of personal mastery during each visit. Pioli (2010) [27] deleted two items of the original scale, because they were not specifically related to carer interactions: 'Sometimes I feel that I'm being pushed around in life' and 'What happens to me in the future mostly depends on me'. The remaining items will be reworded to make them relevant to visits, for example 'I had little control over the things that happened today when I spent time with my family member' and 'I felt helpless in dealing with the problems I experienced during my visit today'.

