### Statistical analysis

We will use independent t-tests to compare the means of outcome measures for the Montessori and control conditions. Next, each outcome measure will be subjected to a 2-way ANOVA with condition (Montessori *vs*. control) as fixed factor. We will then undertake ANCOVAs to investigate whether the intervention enhances certain outcomes (e.g. quality of relationships) after controlling for others (e.g. quality of pre-morbid relationships) to explore the possibility of mediation. Secondly, we will extend these models to examine whether other factors, such as resident-carer relationship (e.g. spouse *vs*. child) and dementia severity (moderate *vs*. severe) serve to moderate treatment benefits. Finally, we will conduct a multilevel variant of these ANOVAs to include higher level factors such as the aged care facility.

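### Baseline resident agitation is collected, and the protocol links it to unsatisfying visits, but no analysis of visit quality names it and the first comparison is unadjusted

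*Protocol article*

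**What the plan says.** The Background section (Protocol article) observes that "visits to the facility can prove unsatisfying, especially if the resident is anxious, agitated and increasingly more confused". The primary measure, under Quality of visits, is what carers report about those visits: "We will ask carers to rate their overall satisfaction with each study visit on a 5-point Likert scale", together with a shortened mastery scale reworded to refer to the visit. The secondary measures are said to be taken at baseline and at the end of the study period. Visit quality is described only as rated at each study visit, so no baseline value for it is described.

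Other measures lists what is collected at baseline. It includes the Clinical Dementia Rating and the "Cohen Mansfield Agitation Inventory [33] with a staff member to establish dementia severity and level of agitation".

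Study design allocates condition by facility. Study protocol says the allocation is made in Excel and mentions no stratification. Under Setting, "The study will be conducted in mainstream and psychogeriatric aged care facilities".

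Statistical analysis sets out a sequence. It begins: "We will use independent t-tests to compare the means of outcome measures for the Montessori and control conditions". An ANOVA with condition as the named factor follows. ANCOVAs then examine outcomes "after controlling for others (e.g. quality of pre-morbid relationships) to explore the possibility of mediation". The models are next extended to see "whether other factors, such as resident-carer relationship (e.g. spouse *vs*. child) and dementia severity (moderate *vs*. severe) serve to moderate treatment benefits". Last, "we will conduct a multilevel variant of these ANOVAs to include higher level factors such as the aged care facility". Agitation is not named at any step.

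**The concern.** By the protocol's own account, an agitated resident makes for a less satisfying visit. Agitation is thus a plausible prognostic factor for the primary measure. It is measured before the intervention by a route that does not depend on the carer who later scores the visits. It matters more than usual here because the common way to gain precision, adjusting for the outcome's own baseline, is not evidently available for visit quality.

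The stated sequence makes no use of it. The first comparison is unadjusted. The covariates that appear later serve mediation or moderation, not adjustment of the main contrast. Whole facilities are allocated, and psychogeriatric and mainstream sites may well differ in mean agitation, so one arm can end up with noticeably more agitated residents by chance. In a trial of 50 carers, such a difference could move the visit-quality result by an amount worth preventing, and the data to prevent it are already being collected.

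**Working it through.** **The plan's own figures.** The protocol gives no figure for agitation and no planned effect size for visit quality. Its sample size (21 per condition at d = 0.80) concerns the Mutuality Scale. It reproduces for a one-sided t-test (power 0.817), but has no bearing on this point. Everything below therefore illustrates size under stated assumptions.

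**Inputs from the protocol.** 50 carers recruited and 20% attrition expected (Sample size calculation), so 50 × 0.80 = 40 analysed. Allocation is by facility.

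**Assumed inputs.**
- Number of facilities k: 4 to 12. The protocol gives no number. Training groups hold up to six carers, but a facility may host several groups, so k cannot be derived.
- ICC of agitation within facility: 0.05 to 0.30.
- Correlation r between baseline agitation and visit quality: 0.3 to 0.5.

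**Step 1, precision.** Adjusting for a covariate with correlation r multiplies residual variance by 1 − r².
- r = 0.3: 1 − 0.09 = 0.91, a 9% reduction.
- r = 0.4: 1 − 0.16 = 0.84, a 16% reduction.
- r = 0.5: 1 − 0.25 = 0.75, a 25% reduction.

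With clustering, the gain also depends on how the correlation divides within and between facilities, so these are guide values.

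**Step 2, chance imbalance.** For N carers in equal arms and m = N/k per facility, the SD of the between-arm difference in mean agitation, in agitation SDs, is √[(4/N) × (1 + (m − 1) × ICC)]. An imbalance of that size shifts the unadjusted contrast by r times that amount, in outcome SDs.

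| N | k | m | ICC | 1 + (m − 1) × ICC | SD of imbalance | r | Shift |
|---|---|---|---|---|---|---|---|
| 50 | 12 | 4.17 | 0.05 | 1.16 | 0.30 | 0.3 | 0.09 |
| 50 | 4 | 12.5 | 0.30 | 4.45 | 0.60 | 0.5 | 0.30 |
| 40 | 12 | 3.33 | 0.05 | 1.12 | 0.33 | 0.3 | 0.10 |
| 40 | 4 | 10 | 0.30 | 3.70 | 0.61 | 0.5 | 0.30 |
| 40 | 10 | 4 | 0.10 | 1.30 | 0.36 | 0.4 | 0.14 |

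The range is 0.09 to 0.30 outcome SDs. These are one-SD imbalances, which about 32% of trials would exceed. The median absolute shift is 0.67 times as large, about 0.06 to 0.20. In the last row, the 1-in-20 shift is 1.96 × 0.144 = 0.28. With 50 carers, the probability that the arms differ by more than 0.5 agitation SDs runs from 10% to 40% over the same range of k and ICC. With no clustering at all it is 8%.

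**Step 3, facility type.** Assume 8 facilities split 4 and 4 without stratification.
- 2 psychogeriatric: the chance that both fall in one arm is 2 × C(6,2)/C(8,4) = 30/70 = 43%.
- 3 psychogeriatric: the chance that all fall in one arm is 2 × C(5,1)/C(8,4) = 10/70 = 14%.

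**Step 4, the multilevel variant.** A facility random effect widens the standard error to reflect variation between facilities. Condition is itself a facility-level factor, so an agitation difference between the two sets of facilities stays in the estimated contrast unless agitation is in the model.

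**The case against.** The strongest reply is that this is a condensed article, that a full covariate list usually belongs in the analysis plan, and that recording a baseline measure without promising to adjust for it contradicts nothing. That is right as far as it goes: there is no contradiction here. The article does, however, state its sequence of analyses and the purpose of its ANCOVAs. The point is that a better main comparison is available than the unadjusted one it puts first.

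Several stronger readings are tempting, and the documents do not support them.
- A reader might infer that agitation is excluded from analysis. Both the covariate and the moderator lists are given as examples, so agitation is unnamed rather than ruled out. An open list still does not pre-specify adjustment.
- A reader might infer that the unadjusted comparison is biased. Facilities are randomised, so it is unbiased in expectation. Variation due to agitation is part of the outcome variance, which a facility-clustered standard error reflects.
- A reader might infer that there are only a few facilities. The number is not given.
- A reader might set the shifts against d = 0.80. That effect size belongs to the Mutuality Scale, a secondary measure.

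It can also be said that the Background names anxiety, agitation and confusion together, without sizes, so choosing agitation alone is a matter of judgement. This partly stands. But no anxiety scale is described, and dementia severity already has a named role as a moderator. Agitation is the feature that is both measured and left without a role.

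**Conclusion.** The point holds as a modest improvement to the analysis of the primary measure, not as an error or contradiction. The protocol links agitation to visit quality and collects it at baseline, yet names it in no analysis and leads with an unadjusted comparison of outcomes that have no described baseline score.

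What is at stake is chance imbalance and lost precision. Both sizes, 9% to 25% of residual variance and a one-SD shift of 0.09 to 0.30 outcome SDs, rest on assumed values of the correlation, the ICC and the number of facilities. Only the 50 recruited and the 20% attrition come from the protocol. If agitation were only weakly related to visit ratings, both would shrink towards nothing. The case that it is related rests on the protocol's own Background statement, which gives no size.

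**What to change.** In Statistical analysis, make the main comparison of visit satisfaction and visit mastery the facility-clustered model, and pre-specify the baseline Cohen Mansfield total as one continuous covariate in it. The unadjusted comparison can stay as a supporting result.

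Use only ratings obtained at baseline, ideally completed before staff know their facility's condition. The protocol does not say whether they will know it when they rate, and the rating is safest as a covariate if they do not.

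The cost is a line of analysis wording and one degree of freedom, with no new data. If ratings are to precede disclosure, the order of the baseline steps at each facility must also be fixed.

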### Sample size calculation

The sample size calculation is based on a study comparing wives caring for moderately impaired husbands that exhibit probable Alzheimer's disease with wives whose spouses demonstrate no mental or physical condition matched on sociodemographic background [34]. We calculated means per group (carers vs. non-carers) for the total Mutuality Scale of the Family Caregiving Inventory [28]. Caregiving wives reported a score of 2.89 and the control participants a score of 3.48 (pooled SD = 0.74), with higher scores indicating a higher quality of the relationship (effect size 0.80). We have used G*Power 3.1.2 (test family = t-test, statistical test = means: difference between two independent means (two groups), alpha = 0.05, power = 0.80 and effect size *d *= 0.80) to calculate that 21 participants in each condition would suffice to reveal such a difference. We estimate 20% attrition and will recruit 50 carers.

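### The sample size rests on a secondary scale and on a carer versus non-carer gap, so the stated 80% power does not describe the primary comparison

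*Protocol article*

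**What the plan says.** **Primary measure.** Under Primary measure, Quality of visits, the protocol article collects two scores at every study visit. The first: "We will ask carers to rate their overall satisfaction with each study visit on a 5-point Likert scale". The second: "In addition, they will complete a truncated version of the Pearlin Mastery Scale", reworded to refer to the visit.

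**Secondary measures.** That section opens: "All of the following secondary measures will be completed at baseline and at the end of the three-week study period". The first of these is the quality of the carer-resident relationship, where the protocol says of carers: "They will also complete the 15-item Mutuality Scale of the Family Caregiving Inventory".

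**Sample size calculation.** The basis is an outside study comparing "wives caring for moderately impaired husbands that exhibit probable Alzheimer's disease with wives whose spouses demonstrate no mental or physical condition". From it: "We calculated means per group (carers vs. non-carers) for the total Mutuality Scale of the Family Caregiving Inventory". The figures are: "Caregiving wives reported a score of 2.89 and the control participants a score of 3.48 (pooled SD = 0.74", giving an effect size of 0.80. The software settings are a t-test for two independent means with "alpha = 0.05, power = 0.80 and effect size" d = 0.80. The result is 21 participants per condition and, allowing for 20% attrition, 50 carers to recruit. Whether the test is one-sided or two-sided is not stated.

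**Trial contrast.** Under Statistical analysis, Montessori is compared with control. Under Participants and Experimental conditions, both groups are family carers of residents with dementia.

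**The concern.** Two things in the calculation do not match the trial it is meant to size.

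- **The outcome.** The calculation concerns a 15-item scale of the overall relationship, completed at baseline and at the end. The primary measure is a rating of individual visits. No difference, SD or power is given for either visit score, and nothing says why an effect size on the relationship scale should carry over to them.
- **The effect.** The 0.80 separates two populations, one living with dementia in a spouse and one not. It does not describe what an intervention did. The trial compares two groups of dementia carers over six sessions in three weeks, and the control group receives a three-hour education session of its own.

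What is at stake is how the result will be read. If visit quality shows no significant difference, a reader who sees 80% power may take this as good evidence against a useful effect. The document establishes no power for that outcome.

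**Working it through.** **Inputs from Sample size calculation:** means 2.89 and 3.48, pooled SD 0.74, alpha 0.05, power 0.80, 21 per arm, 20% attrition, 50 recruited. Power and sample size use the exact two-sample t-test (noncentral t).

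**Step 1. Effect size.** 3.48 − 2.89 = 0.59 points; 0.59 / 0.74 = 0.797, which agrees with the stated 0.80.

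**Step 2. The stated 21 per arm.** At d = 0.80, alpha 0.05 and power 0.80:

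- one-sided: n = 20.03, rounded up to 21 per arm, as stated;
- two-sided: n = 25.5, rounded up to 26 per arm.

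The stated figure therefore reproduces only as a one-sided test.

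**Step 3. Completers.** 50 × (1 − 0.20) = 40, or 20 per arm. This is slightly below the 42 the calculation asks for; keeping 42 would need 42 / 0.80 = 52.5, so 53.

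**Step 4. Power with 20 per arm, carers treated as independent.** Only d = 0.80 comes from the document. The value 0.40 is half of it (0.59 / 2 ≈ 0.30 points), and both 0.40 and 0.50 are assumptions for illustration.

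| d | Origin | One-sided 5% | Two-sided 5% |
|---|---|---|---|
| 0.80 | whole gap | 80% | 69% |
| 0.50 | assumed | 46% | 34% |
| 0.40 | half the gap, assumed | 34% | 23% |

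At each d the two columns differ by about 11 to 12 points. That difference is the effect of sidedness alone; the fall down each column is the effect of a smaller treatment benefit.

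**Step 5. Difference detectable with 80% power, 20 per arm, no clustering.** 0.91 SD two-sided; 0.80 SD one-sided.

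**Step 6. Allowing for randomisation by facility.** The document gives neither a facility count nor an intracluster correlation (ICC). Assume 5 completing carers per facility and an ICC of 0.01 to 0.10. The design effect is 1 + (5 − 1) × ICC, and the effective number per arm is 20 divided by it.

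| ICC (assumed) | Design effect | Effective n per arm | Detectable difference, two-sided |
|---|---|---|---|
| 0.01 | 1.04 | 20 / 1.04 = 19.2 | 0.93 SD |
| 0.10 | 1.40 | 20 / 1.40 = 14.3 | 1.09 SD |

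Forty completers at 5 per facility means 8 facilities. An analysis that takes its degrees of freedom from the facilities would have fewer than are used here, so this range leans to the favourable side.

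**The case against.** The strongest defence has three parts.

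**A standardised effect can be carried across scales.** With a given number per arm, d = 0.80 gives the same power on any roughly normal score. The Mutuality Scale also overlaps with visit quality, since one of its example items asks about enjoyment of time spent together. Averaging ratings over several visits may reduce noise. This stands against any claim that the calculation tells the reader nothing about the primary measure. It does not supply the missing step, which is a reason to expect 0.80 SD on the visit scores.

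**The document treats large effects as plausible.** The Background cites effects of 0.5 to 1.15 for non-drug treatments, and large gains in confidence from a carer-delivered programme in the community. But the first range concerns residents' behavioural and psychological symptoms, not carers' outcomes, and the second comes with no figure. Neither is used in the sample size section.

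**The low-power figures are illustrations.** This is right. No passage gives d = 0.40 or 0.50 for any carer outcome, and the true power for the visit scores cannot be calculated from this document.

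A reader might also infer that two primary scores, each tested at 5%, inflate the chance of a false claim of success. The article does not support that as a finding. It states no rule under which either score alone counts as success, and such a rule is commonly left to a statistical analysis plan, which is not shown here.

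**Conclusion.** The point holds. The calculation that sets the recruitment target concerns a secondary scale and a between-population gap, and no link to quality of visits is argued. This is a fault in what is written, not a detail deferred to another document: the scale, means, SD, settings and result are all stated.

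On the Mutuality Scale, 80% power is numerically equivalent to closing the whole 0.59-point gap. A reader might infer that the authors expect such a complete recovery; they do not say so.

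With 40 completers treated as independent, power for the whole gap is 80% one-sided or 69% two-sided. For half the gap it is 34% or 23%, and that fraction is an assumption. A reader might take 23% as the trial's power on its primary measure. That would be wrong: it refers to the secondary scale, to a two-sided test that the stated 21 does not reproduce, and to an assumed effect. For the primary measure the defensible statement is the detectable difference: 0.91 SD two-sided or 0.80 SD one-sided before clustering, and about 0.93 to 1.09 SD two-sided under the assumed facility size and ICC.

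**What to change.** Revise the sample size section as follows:

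1. Say that the calculation applies to the Mutuality Scale, a secondary measure, and that d = 0.80 is the full gap between dementia carers and non-carers rather than an expected intervention effect.
2. State whether the test is one-sided or two-sided. If it is two-sided, 21 per arm does not give 80% power at d = 0.80.
3. Replace the 80% power claim with the standardised difference in the primary visit score that 40 completers can detect: about 0.91 SD two-sided (0.80 one-sided) ignoring clustering, followed by a range for clustering with the assumed carers per facility and ICC written beside it.
4. Describe the trial as exploratory for effects smaller than that.

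The cost is a change of wording and a less favourable statement of power. No extra carers are needed.

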Interventions to alleviate carer stress and BPSD have mostly treated carers and relatives separately rather than focusing on re-establishing and enhancing their relationship. Since one-to-one structured activities have been shown to reduce BPSD and also improve the caring experience, they seem an ideal intervention to bring people together and thus improve wellbeing for both carers and their relatives with dementia. The current study will investigate the effect of individualised activities based on the Montessori methodology administered by family carers in residential care on the wellbeing of carers. We hypothesise that family carers conducting Montessori-based activities will experience higher self-rated mastery, fewer depressive symptoms, and a better quality of life than carers in a waiting list period, as well as a better quality of visits and overall relationship with the resident.

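### The 21 carers per condition come from an undeclared one-tailed t-test (a two-sided test needs 26), and recruiting 50 with 20% attrition leaves 40 completers, not 42

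*Protocol article*

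**What the plan says.** Everything on this point is in two sections of the protocol article.

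**Sample size calculation.** The effect comes from an external comparison of caregiving and non-caregiving wives on the Mutuality Scale: "Caregiving wives reported a score of 2.89 and the control participants a score of 3.48 (pooled SD = 0.74"), summarised as "effect size 0.80". The settings, for a t-test, are reported as "statistical test = means: difference between two independent means (two groups), alpha = 0.05, power = 0.80" together with that effect size, and the result is 21 per condition, or 42 in total. The recruitment target follows: "We estimate 20% attrition and will recruit 50 carers". The number of tails is not among the reported settings.

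**Statistical analysis.** The first analysis is "We will use independent t-tests to compare the means of outcome measures for the Montessori and control conditions", again with no number of tails. Each outcome then goes into an ANOVA with condition as a fixed factor, followed by ANCOVAs and a multilevel version that brings in the facility.

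The Background states the hypotheses in a direction, for example that carers in the Montessori arm "will experience higher self-rated mastery, fewer depressive symptoms, and a better quality of life than carers in a waiting list period". It does not declare a one-sided test.

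**The concern.** A reader who sees alpha of 0.05 for a two-group t-test with nothing said about tails will normally assume a two-sided test. On that assumption 21 per condition is too few for d = 0.80, and the stated 80% power would belong to a test other than the one the reader expects. The ANOVAs planned on the same outcomes raise the same issue, because an F-test has no direction.

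The recruitment target also looks inconsistent with the calculation that precedes it. Losing 20% of 50 leaves fewer completers than the 42 asked for.

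At stake is the meaning of a null result. If power is nearer 70% than 80%, the chance of missing the planned effect is about half as large again as the article implies. The reader cannot tell which figure applies.

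**Working it through.** **Inputs, all from the Sample size calculation section:** means 2.89 and 3.48, pooled SD 0.74, d = 0.80, alpha 0.05, target power 0.80, 21 per condition, 20% attrition, 50 recruited. Equal arms are assumed.

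**Step 1: effect size.** (3.48 − 2.89)/0.74 = 0.59/0.74 = 0.797, which rounds to the stated 0.80.

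**Step 2: the plan's own figure.** For n per arm, the two-sample t statistic has 2n − 2 degrees of freedom and noncentrality d × √(n/2). Power is the probability that this noncentral t exceeds the critical value at 1 − 0.05 (one-tailed) or, in absolute value, at 1 − 0.05/2 (two-tailed). With d = 0.80:

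| n per arm | df | noncentrality | critical t, one-tailed | power, one-tailed | critical t, two-tailed | power, two-tailed |
|---|---|---|---|---|---|---|
| 20 | 38 | 2.530 | 1.686 | 79.9% | 2.024 | 69.3% |
| 21 | 40 | 2.592 | 1.684 | 81.7% | 2.021 | 71.6% |
| 25 | 48 | 2.828 | 1.677 | 87.4% | 2.011 | 79.2% |
| 26 | 50 | 2.884 | 1.676 | 88.5% | 2.009 | 80.7% |

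The smallest n that reaches 80% is 21 one-tailed and 26 two-tailed. The printed 21 is therefore exactly the one-tailed answer. Using the unrounded d of 0.797 gives the same two sample sizes. A normal approximation gives 20 and 25, so the choice of method does not explain the difference.

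**Step 3: the ANOVA.** With two conditions, the F-test for condition has F = t², so it is equivalent to the two-tailed t-test. Its power at the same effect is 71.6% with 21 per arm and 69.3% with 20. This applies to a comparison of condition alone. The article calls the ANOVA two-way but names only one factor, so any gain from a second factor cannot be computed from it.

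**Step 4: attrition.** To finish with N completers after a loss of 20%, recruit N/(1 − 0.20).

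- 42/0.80 = 52.5, so 53, or 54 for equal arms.
- 42 × 1.20 = 50.4, which is close to the stated 50 and suggests multiplication by 1.2 in place of division by 0.8.
- 50 × 0.80 = 40 completers, or 20 per arm, which is two fewer in total than 42.

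**Step 5: the two readings at 20 completers per arm.**

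- One-tailed: 79.9%, so the chance of missing the effect is 20.1%.
- Two-tailed: 69.3%, so the chance of missing the effect is 30.7%.

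**Step 6: what 80% two-sided would need.** 2 × 26 = 52 completers; 52/0.80 = 65 recruited, or 66 for equal arms.

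None of these figures allows for randomisation by facility.

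**The case against.** The strongest reply is that nothing printed is false. The article never says the t-test is two-sided, its hypotheses are directional, and with one tail its inputs return 21 exactly. The ANOVAs come after the t-tests and were not the basis of the calculation, so they do not show that the t-tests are two-sided. This is also a condensed article, and the number of tails may be stated in a fuller document.

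Much of that stands. A reader might infer that the 80% power fails on the plan's own inputs, or that the risk of missing the effect simply is 31% and not 20%. The article does not support either statement without a condition, because both require a two-sided test that it does not specify. Nor does the attrition slip break the power claim on the reading that produced 21: one-tailed power falls only to 79.9%.

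Three things remain. A directional hypothesis says what the investigators expect; it does not declare a one-sided test. The article prints its settings and its result, and the result depends on a setting it leaves out, so this is more than detail deferred to another document. And the 80% does not carry over to the non-directional F-tests for condition, whichever tail the t-tests use. The shortfall from 42 to 40 completers needs no assumption about tails.

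**Conclusion.** The point holds as an undeclared one-tailed calculation plus a separate small inflation error.

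- **Tails.** 21 per condition is the one-tailed answer; the conventional two-sided test and the F-test for condition need 26.
- **Size.** With the 20 per arm expected to complete, power is about 69% two-sided and about 80% one-tailed. The tail accounts for nearly all of the difference.
- **Attrition.** The target of 50 delivers 40 completers and not 42. On the one-tailed reading this costs under two percentage points (81.7% to 79.9%).

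The figures assume equal arms, d = 0.80 on the Mutuality Scale, exactly 20% loss in each arm and independent observations. The Mutuality Scale is listed among the secondary measures, so they do not describe power for quality of visits, the primary measure. Any design effect for facility would lower all of them.

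**What to change.** Keep 50 carers. State the number of tails in both the Sample size calculation and the Statistical analysis sections so that they agree, and give the expected number of completers as 40 (20 per arm). Then use one of two consistent versions.

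- **If two-sided:** state power of about 69% for d = 0.80 on the Mutuality Scale, before any design effect for facility. It may help to add that 80% would need 52 completers, or 65 to 66 recruited.
- **If one-sided:** declare it in both sections, state that 50 recruits give about 80% power for the t-test before clustering, and note that the F-tests for condition have about 69% at the same effect.

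The two should not be mixed: 42 is the one-tailed total, so inflating it to 53 does not go with a two-sided power statement. The cost is a few sentences. Recruitment does not change, and the only downside is a less favourable stated power, for the t-tests if they are two-sided and for the F-tests in either case.
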